### Blinding

Allocation of interventions cannot be concealed from either training staff or study participants once implementation occurs. However, all data collectors will be blinded to the intervention status of preschools. The study will be presented as a project related to family health and wellbeing, no specific study hypotheses will be presented to participants, and data collectors will not be involved in delivering the intervention. However, parents at preschools receiving the intervention will be aware of the training activities, and may still link the intervention to survey activities.

The possibility of parents from a control group preschool changing to an intervention group preschool at different stages (pre or post intervention) of the study in order to receive the intervention, will be minimised by the intervention being implemented after preschool enrolments have been completed for the school year. Participants from control areas may also obtain information on service use through interaction with intervention area households, or through having siblings attending control and intervention area preschools. To assess the degree to which this may occur, we will collect data on participant households preschool enrolment details, residence and sources of information and utilisation of intervention-relevant services.

### Data collection

Data from parents will be collected in de-identified form through anonymous, self-administered surveys. Literacy rates in Sri Lanka are very high for both men and women, so we do not expect illiteracy to be a barrier to participation. Data collection will be supervised by staff recruited specifically for this task. These staff will receive training prior to commencement of the baseline data collection which address the contents of the survey and how to provide confidential, safe and appropriate support to participants who seek or request assistance, including for domestic violence or substance misuse, during completion of the survey. Refresher training will be provided to the same team prior to the collection of post intervention data.

All government preschools in the study areas will be involved in the following data collection activities:A baseline survey of mothers and fathers at the beginning of the preschool year (January 2018)A follow up survey of all mothers and fathers at the end of the preschool year (December 2018).

Preschools receiving the intervention will participate in the following additional post intervention data collection activities:Qualitative interviews with key participants including teachers, community members, community development staff and other government sector service providers to determine their satisfaction with the intervention, and any challenges or barriers to its implementation.

### Capacity building intervention

We aim to implement a community-based support program delivered by preschool teachers and volunteer parents that will increase awareness, knowledge and uptake of available services for IPV and substance misuse, and of the link between these issues and poorer education outcomes in children. Through this, we aim to decrease the prevalence of IPV and substance misuse.

The intervention design was developed prior to delivery of the baseline survey through discussions and  workshops attended by government service providers, including welfare, health, policing, substance misuse and education providers. These workshops demonstrated the availability of a comprehensive range of services across IPV, substance misuse and other social services. A key finding from these workshops was the need for improved links between such services and the community, in particular the need to more effectively engage men. Another important finding was that promoting children’s education was considered a promising route through which to encourage positive behaviour change.

The following specific activities and interventions will be implemented in the intervention preschools: Capacity building, training and support to selected mothers on the provision of safe, confidential and relevant community-based referral and support services to women affected by IPV; Capacity building, training and support to selected frathers on the provision of safe, confidential and relevant community-based referral and support to men seeking support for substance misuse problems; Capacity building and on-the-job training and support to preschool teachers on provision of IPV and substance misuse prevention educational messages (including the links between these issues and poor child development [1]), and referral pathways to sevices for these issues. The training intervention will be delivered after completion of the baseline survey and randomisation (see Fig. 1).  Training for mothers will focus on what IPV services are available and how to access them. These trained community members will work with those mothers experiencing IPV to: define which health, safety, protection and justice goals they are seeking in accessing services; ensure they are aware of how to access services relevant to these goals; and support them in the often drawn-out process of achieving these goals. The value of such programs in supporting those affected by IPV suggests they may also be an effective means of supporting uptake of substance misuse support services for fathers in the same way.

Training is essential to ensure these community members have the skills and knowledge to provide safe, non-judgmental and confidential information and ongoing support. Training and resource materials will be developed through workshops with local service providers, with input from technical experts including social workers, psychiatrists and psychologists experienced in addressing IPV and substance misuse in Sri Lanka and internationally. These will cover information on available services for IPV and substance misuse including contact details, referral criteria, duration of available programs, expected commitment of participant, costs of services and likely impact of benefit outcomes of accessing services.

The training team, responsible for delivering the intervention, will include local experts involved in developing the training materials who have expertise in providing services to families and individuals affected by substance misuse and IPV. Training will focus on non-judgemental support and will be delivered in the local language of the community on separate dates to, and after completion of, baseline surveys.

Materials developed for this study will build on and adapt existing resources developed locally and internationally shown to have value in multiple settings, including those with limited resources. Such training interventions include those utilised in community-based advocacy and support services [8], and community mobilization interventions developed to prevent violence against women [1, 2].

Through the training of selected fathers in the preschool community a similar model will be applied to ensure that those needing support for substance misuse are aware of available services and how to access them, and complete substance abuse programs.

Discussions with stakeholders identified the need for preparatory community outreach activities in order to familiarise the community with the project team. These activities were considered necessary to effectively engage the study communities, in particular men, to support good uptake of the intervention. These community engagement activities will commence in both study areas prior to implementing the intervention and will target the community as a whole (regardless of their status as intervention or control preschool areas). Activities will be developed based on the experience of service providers working for several years in these areas and include general health, sanitation and education related information and resources, delivered at community meetings by members of the project team.

The impact of community-based support and advocacy to address IPV and substance misuse is dependent on how effective such interventions are in mobilising existing services, in particular government health, policing, justice and welfare services. In each study area designated government Community Development Officers (CDOs) manages all of the government preschools in that area. The role of the CDOs include regular meetings with preschools and oversight of local-level livelihood programs and other welfare services. By including the CDOs in this capacity building intervention, we will strengthen the link between preschools and government service providers who are well placed to ensure access to longer-term support for families.

Our intervention is broadly structured to address the different stages of behaviour change and decisional balance [10]. Linking positive behaviour change to the educational success of preschool children is designed to move individuals from the stages of pre-contemplation to contemplation by influencing the way individuals assess the pros and cons of particular behaviours. Providing trusted sources of peer-support and information is designed to support individuals to move through the stages of preparation, action and maintenance of behaviour change by supporting increased self-efficacy.

In developing, designing and implementing the intervention, our work was underpinned by a framework of community engagement based on the following principles: a shared vision; mutual respect; awareness; shared responsibility; building capacity; improved coordination; inclusiveness; appropriate timeframe; sustainability; and integrity [11].

### Outcome measures

Of interest are differences at 10 months post-intervention between families in control and intervention groups in:the primary outcome: experience of intimate partner violence by mothers in this group measured using instruments developed and validated across multiple countries for the World Health Organization (WHO) multi-country survey of violence against women [12] ^.^andsecondary outcomes of interest:◦ Prevalence of substance misuse in fathers in this group measured via the locally adapted Alcohol Use Disorders Identification Test (AUDIT) [13] and the Drug and Alcohol Screening Test (DAST) [14]; and◦ Awareness and uptake of services for IPV and substance misuse measured through locally-relevant tools developed during initial project workshops.

Process measures that will be assessed through interviews in intervention areas include:Teachers’ and volunteer mothers’ knowledge and skills in regards to the initial assessment, management and referral of families affected by IPV.Volunteer fathers’ knowledge and skills in the initial assessment, management and referral of families affected by substance misuse.Community and service provider satisfaction with the intervention, assessed through key informant interviews with community development staff and government service providers (health, welfare, police etc)

#### Other factors to be assessed

Factors identified as associated with IPV and substance misuse in previous research include socio-economic status, educational status, age, marital status and mental health. Data on these factors will be collected, including on mothers’ and fathers’ mental health and depression using a locally developed and validated screening tool for depression (the Peradeniya Depression Scale) [15]. We also postulate that family and community functioning, including measures of social cohesion and inclusion, may be associated with the outcomes of interest. These will be assessed through locally adapted indicators and rating scales measuring family and children’s resilience [16].

#### Sample size

The sample size was calculated to demonstrate a significant difference in the proportion of mothers of preschool children reporting exposure to IPV following intervention. We plan to recruit at least 34 preschools, with 20 families per preschool, for a total of 680 potential families (which equates to 340 families in the intervention group and 340 in the control group who may be approached to participate in this study. We anticipate minimal loss to drop out due to the educational focus on children this study promotes.

We assumed a participation rate of 90%, based on past research which found a consent rate in this population for domestic-violence related surveys of 97% [3]. We therefore expect a sample size of approximately 612 families, or 306 per group. Based on a design effect due to correlation of outcomes within preschools of 1.5 (which equates to an intra-class correlation coefficient of 0.025), 80% power, a 5% significance level and a pre-intervention 12 month prevalence of IPV of 40% [3] we will be able to detect a difference in post intervention 12 month prevalence of IPV between intervention and control groups of 15%.

There are no intervention studies in Sri Lanka or that region that examine the effects of community-based interventions. However, an extensive community-based intervention (SASA!) in Uganda, Africa reported a 53% reduction in physical IPV reported by women in the intervention group [17]. Therefore, we consider it justifiable to expect an intervention effect of at least 15%.

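### The sample size inputs give about 90% power for 15 percentage points, or about 13 points at 80% power, not 15 points at 80% as stated

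*Protocol article*

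**What the plan says.** All of the relevant text is in the Sample size section of the protocol article.

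- **Numbers:** 34 preschools with 20 families each (680) and 90% participation. "We therefore expect a sample size of approximately 612 families, or 306 per group".
- **Clustering:** "a design effect due to correlation of outcomes within preschools of 1.5 (which equates to an intra-class correlation coefficient of 0.025").
- **Error rates and baseline:** "80% power, a 5% significance level and a pre-intervention 12 month prevalence of IPV of 40" (percent). The section does not say whether the test is one-sided or two-sided.
- **Result:** "we will be able to detect a difference in post intervention 12 month prevalence of IPV between intervention and control groups of 15" (percent).
- **Justification:** a community intervention in Uganda is cited as having reduced physical IPV by 53%, followed by "Therefore, we consider it justifiable to expect an intervention effect of at least 15" (percent). Neither percentage is labelled as absolute or relative.

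**The concern.** The section prints every input except sidedness, so its result can be checked, and the check fails. Readers will use this statement to interpret the primary result, particularly a null one. As written, they cannot tell whether the trial was planned with 80% or about 90% power for 15 points, or whether it holds an undeclared margin.

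Two smaller faults sit beside it. The 15% and the 53% stand next to each other without scale labels, so the planned effect looks more modest beside the cited one than it is. And the design effect is said to equate to an ICC that gives a slightly smaller value at the article's own cluster sizes.

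**Working it through.** **Inputs (all from Sample size unless noted).** n = 306 per arm; design effect 1.5; power 80%; significance 5%, taken as two-sided (assumption); control prevalence 40%, taken to stay at its pre-intervention value (assumption). The 15% is worded as a difference in prevalence between groups, so it is read as 15 points: 40% vs 25%. Allocation is 1:1 (Randomisation).

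**Step 1: effective size.** 680 × 0.9 = 612, or 306 per arm, as stated. 306/1.5 = 204 effective mothers per arm.

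**Step 2: try to reproduce 15 points at 80% power.** Pooled-variance formula for two proportions, with p̄ = (0.40 + 0.25)/2 = 0.325:

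n = [1.96·√(2·0.325·0.675) + z_power·√(0.40·0.60 + 0.25·0.75)]² / 0.15²

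The two square roots are 0.6624 and 0.6538.

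- 80% power (z = 0.8416): (1.298 + 0.550)²/0.0225 = 151.9, about 152; × 1.5 = 228 per arm.
- 90% power (z = 1.2816): (1.298 + 0.838)²/0.0225 = 202.8; × 1.5 = about 304 per arm.

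The stated 306 matches the 90% requirement, not the 80% one.

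**Step 3: power at the stated size.** z = (0.15·√204 − 1.298)/0.6538 = (2.142 − 1.298)/0.6538 = 1.29, so power is 90.2%.

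**Step 4: detectable difference at 80% power.** Solving the same formula with n = 204 gives 13.05 points, that is 40% vs about 27%.

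**Step 5: other conventions.**

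| Convention | Power for 15 points | Difference at 80% power |
|---|---|---|
| Pooled, two-sided | 90.2% | 13.05 |
| Continuity correction | 88.2% | 13.5 |
| t reference, 32 df | 88.8% | 13.3 |
| Increase instead of decrease (40% vs 55%) | 86.1% | 13.8 |
| Increase, continuity correction | not computed | 14.3 |
| Design effect 1.425 (ICC 0.025, 18 per preschool) | 91.6% | 12.7 |

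A one-sided test raises power for 15 points to 94.6%. None of these returns 15 points at 80%. To get there with 306 per arm, the design effect would have to be 306/152 = 2.01, an ICC of 1.01/17 = about 0.06 at 18 per preschool, against the stated 1.5 and 0.025.

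**Step 6: room for missing outcomes.** 228/306 = 74.5%. Holding the design effect at 1.5, 15 points keeps 80% power with up to about 25% of primary-outcome data missing.

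**Step 7: scale.** 15/40 = a 37.5% relative reduction. A 53-point fall is impossible from 40%, so in this setting 53% can only be relative: 0.53 × 40 = 21.2 points, to 18.8%. Like for like, the comparison is 37.5% with 53%, or 15 points with 21.2.

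**Step 8: design effect.** 1 + (20 − 1) × 0.025 = 1.475; 1 + (18 − 1) × 0.025 = 1.425.

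**The case against.** **The error does no harm.** The article says the trial can detect 15 points at 80% power. On its inputs it can, with room to spare, and understated power makes a reader more cautious about a null result. This stands: it settles the direction and limits the weight of the point. It does not make the printed figures agree with each other.

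**The gap may be a deliberate margin.** The primary analysis is complete-case (Data analysis), mothers may hand in the questionnaire without the violence sections (Ethical considerations), and those who miss a survey cannot be followed up (Discussion). About 25% missing would bring power for 15 points down to about 80%. But the section claims no such margin; it expects minimal loss. The argument does not rescue the derivation, but it is a good reason not to print 90% power without a condition.

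**Stronger readings that a reader might infer, and that the article does not support:**

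- *The trial is underpowered because 15% is relative.* For 40% vs 34% power would be only 24%. But the text describes a difference in prevalence between groups, which is absolute.
- *The cited 53% undermines the planned effect.* It exceeds the planned effect on either scale (Step 7). What is missing is a label. The cited figure also concerns physical IPV only.
- *The ICC and design effect contradict each other.* At 20 families 1.475 rounds to 1.5, and using the exact value moves the detectable difference further from 15, so this does not explain the gap.
- *The power was really meant to be 90%.* The match (304 vs 306) is suggestive, but only the sponsor can say.

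**Conclusion.** The statement is wrong as written, in the conservative direction. With 306 mothers per group and a design effect of 1.5, the trial has about 90% power for 15 percentage points (88% to 90% across the two-sided methods tried for a reduction at that design effect), or 80% power for about 13 points. The stated pairing of 80% with 15 points needs only about 228 per arm.

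This rests on a two-sided 5% test, a control prevalence that stays at 40%, the stated design effect, and primary-outcome data from all 306 mothers per group. The arithmetic is firm. The scale labelling and the rounding of the design effect are minor points of presentation. Nothing here shows the sample to be too small for its stated target.

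**What to change.** Restate the result in the Sample size section along these lines: with 306 mothers per group, a design effect of 1.5 and a two-sided 5% test, the trial has 80% power to detect an absolute difference of about 13 percentage points (40% vs 27%), or about 90% power for 15 percentage points (40% vs 25%, a 37.5% relative reduction), if primary-outcome data are obtained from all 306 mothers per group.

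If the sponsor meant the gap as a margin for missing outcomes, keep 15 points at 80% power and say so, adding that it holds with up to about 25% missing.

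In the same edit:

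- label the 15% as percentage points and set it against the 53% reduction on one scale, noting that the 53% is read as relative;
- keep the ICC of 0.025 and describe 1.5 as rounded up from 1.475 (20 per preschool) or 1.425 (18).

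The cost is rewording only, with no change to enrolment, design or analysis.

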#### Data management and quality assurance

Data will be entered into password-protected data management software by data entry staff during both survey rounds (baseline and follow-up) and will be assessed for quality using standard queries in the software package. Any issues in data quality will be identified and addressed through discussions between the data collection team and project supervisors in the field. Hardcopies of completed surveys will be stored securely for five years at the study co-ordinating site. Data will be accessible to the study investigators as per the conditions of the ethical approvals. Any additional individuals within or external to the study requesting access to the study data will be required to apply to the ethical review committees.

#### Data analysis

The main analysis will be by intention-to-treat. The primary analysis will be a regression model of IPV experienced by mothers within the past 10 months in the intervention group, adjusted for other potential confounders, and correlation of outcomes within preschools using a Generalised Estimating Equations approach. Primary analysis will be a complete case analysis.

Similar analysis will be conducted for secondary outcomes including prevalence of substance misuse in fathers and awareness and uptake of services for IPV and substance misuse. Secondary analysis will use multiple imputation. Sensitivity analysis will be conducted through secondary adjusted analysis accounting for potential confounders. Confounders specified a priori as being potentially associated with the outcome include age, mental health status and socio-economic status.

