## Discussion

It is not possible to blind participants to the intervention and, as outcomes are self-reported, there is the potential for bias on the part of participants, particularly if participants are able to link the intervention to the surveys through which outcomes will be quantified. To address this, the data collection team will be completely separate from the training team who deliver the intervention, and participants will not be informed of a link between these two activities. The data collection team will also be blinded to whether participants are from intervention or control preschools.

The preschool setting limits the time available to evaluate the intervention. Children usually attend preschool for one year. Our follow up surveys must be completed by the end of the school year (December 2018) otherwise participants will be lost to follow up as no contact details are collected. This provides us with a maximum of ten months to evaluate our intervention. Past research has shown that positive effects from community interventions may not be reported until later follow up of 24 months [8].

No identifying data will be collected. Therefore there is no possibility of following up any participants who drop out of training or do not complete either survey.

Our research is limited to urban areas and may not be generalised to rural areas. As a separate component of this study, we are also piloting the program in three rural preschools. Levels of service provision are generally lower in such areas and, through this pilot, we aim to determine the adaptations required to successfully implement a similar program in rural areas of Sri Lanka. Qualitative data will be collected in the rural preschools to determine the feasibility, acceptability and adaptations necessary for implementation of this intervention in rural areas. Data will be collected through interviews with all teachers and mothers and fathers who participated from each of the three preschools.

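### The primary outcome has two recall windows: the trial is sized on 12-month IPV prevalence but analysed on the past 10 months, and only the 10-month window can fit the period after training

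*Protocol article*

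**What the plan says.** All references are to the protocol article.

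- **Sample size:** the planning rate is "a pre-intervention 12 month prevalence of IPV of 40" per cent. The same sentence applies that window to the comparison between arms: "we will be able to detect a difference in post intervention 12 month prevalence of IPV between intervention and control groups of 15" per cent.
- **Data analysis:** the primary model is a regression of "IPV experienced by mothers within the past 10 months in the intervention group".
- **Outcome measures:** "Of interest are differences at 10 months post-intervention between families in control and intervention groups". This gives a time point but no recall window.
- **Data collection:** the baseline survey is in January 2018 and the follow-up survey in December 2018.
- **Capacity building intervention:** "The training intervention will be delivered after completion of the baseline survey and randomisation".
- **Discussion:** "This provides us with a maximum of ten months to evaluate our intervention".

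**The concern.** The primary outcome depends on how far back a mother is asked to look. The sample-size statement uses 12 months for the comparison after the intervention, so its 12 months is not merely a feature of the source of the 40%. The analysis uses 10 months. Nothing in Outcome measures decides between them.

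Two things follow. If the December question asks about 12 months, it covers time before training began. Violence in that time makes a mother a case in either arm and cannot be prevented by the training, so the contrast shrinks. If the question asks about 10 months, the 40% and the 15 points describe a different quantity from the one analysed.

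A wrong question would be hard to repair afterwards. The surveys are anonymous and no contact details are kept, so mothers cannot be asked again.

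**Working it through.** **1. Timeline.** A 12-month look-back from December 2018 starts in about December 2017, before the January baseline and so before training. With at most ten months of evaluation, at least about 12 − 10 = 2 months of that window precede training.

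**2. The plan's own figure.** Inputs from Sample size: 306 mothers per arm, design effect 1.5, 80% power, 5% significance (taken as two-sided), 40% prevalence. The 15% is read as percentage points, 40% to 25%, and the 40% is carried to controls at follow-up.

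- Effective n per arm = 306 / 1.5 = 204.
- With p̄ = (p1 + p2)/2, z = [|p1 − p2|·√n − 1.96·√(2p̄(1 − p̄))] / √(p1(1 − p1) + p2(1 − p2)), and power = Φ(z).
- For 40% v 25%: z = (0.15 × 14.283 − 1.96 × 0.662) / 0.654 = 1.29, so power is about 90%.
- 80% power needs 152 per arm before clustering, and 152 × 1.5 = 228. With 306 per arm, the smallest difference detectable at 80% power is 13.1 points.

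The stated 15 points therefore corresponds to about 90% power. The plan's statement is conservative, and that slack matters below.

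**3. The 10-month window (Data analysis).** The article gives no 10-month rate, so a range is needed. The same relative reduction is kept: 15/40 = 37.5%.

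| Assumption | Control | Intervention | Power |
|---|---|---|---|
| Proportional to time: 40 × 10/12 | 33.3% | 20.8% | 81% |
| Constant hazard: 1 − 0.6^(10/12) | 34.7% | 21.7% | 83% |
| Nearly all IPV persistent | 40% | 25% | 90% |

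**4. The 12-month window (Sample size), two pre-training months, evenly spread onset (assumed).** Control stays at 40%.

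- *Effect applied to the post-training 10-month rate.* The two-month rate is 1 − 0.6^(2/12) = 8.2%. Intervention arm: 1 − (1 − 0.082)(1 − 0.217) = 28.1%. The difference is 11.9 points and power is about 72%.
- *Effect applied to the hazard.* Control hazard is −ln(0.60)/12 = 0.0426 per month and intervention hazard is −ln(0.75)/12 = 0.0240. Intervention arm: 1 − exp(−(2 × 0.0426 + 10 × 0.0240)) = 27.7%. The difference is 12.3 points and power is about 75%. With three pre-training months it is 10.9 points and 64%.

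**The case against.** The strongest reply is that the analysis section is the only place that defines the analysed variable, and it says 10 months. Outcome measures and the Discussion point the same way. On this reading the sample-size sentence simply kept the window of the study that supplied the 40%, and power on the 10-month window stays above the stated 80%. This largely stands. It confines the fault to a mismatch between the sizing statement and the analysis. It does not remove the fault, because the sizing statement names the post-intervention comparison itself. Nor can the two harms both be large. If IPV is mostly persistent, the 10- and 12-month rates nearly coincide and 40% remains a fair planning rate. If onset is evenly spread, the dilution is moderate.

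Three stronger readings are tempting, but the article does not support them.

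- **That power collapses.** If 20% or 25% of all mothers were already exposed in the two pre-training months, the 12-month contrast would be 0.375 × (40 − 20) = 7.5 or 0.375 × (40 − 25) = 5.6 points, with power about 35% or 22%. This needs both a 12-month analysed outcome, contrary to Data analysis, and half or more of a year's cases to be exposed within two months. The article gives no such share.
- **That the 10-month look-back also reaches before training.** It would if training ended later than about February. The text gives no end date, and the timeline figure to which it refers is not shown.
- **That the primary endpoint is undefined.** Data analysis does name one window.

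**Conclusion.** The inconsistency is real and stands in current text. Its consequence depends on which window the December questionnaire uses, and the questionnaire is not shown.

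- **10 months, as in the analysis section:** the planning rate should be restated, but the trial keeps about 81–90% power for the planned relative reduction.
- **12 months, as in the sample-size section:** about two or more pre-training months enter the outcome in both arms. With evenly spread onset, power falls below the stated 80%, to about 72–75% with two such months. The bias is towards no difference, so it cannot create a false benefit. Recurrent violence would enlarge the dilution, but the article gives nothing from which to size that.

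These figures rest on 204 effective mothers per arm, a 37.5% relative reduction, 40% 12-month prevalence in controls at follow-up, and the stated onset patterns. The contradiction itself rests on none of them.

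**What to change.** State one recall window for the primary outcome in Outcome measures, Sample size and Data analysis. It should not extend before the intervention, so it should be no longer than ten months, and it should use the same calendar reference in both arms. The sponsor should take the start of the window from its own training timeline, since the text describes separate training for mothers, fathers and teachers and gives no single end date.

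Keep any 12-month item as a secondary outcome, for comparison with baseline and earlier research.

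Restate the planning prevalence and detectable difference for the chosen window. For ten months, with 204 effective mothers per arm and 80% power, the smallest detectable difference is about 12.3 points from 33.3%, 12.5 points from 34.7% and 13.1 points from 40%.

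The cost is small: a reworded sample-size sentence, a planning prevalence that may be slightly lower, and possibly one changed question stem in the December survey. The change has to be made before that survey is run.
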